### Randomization and Blinding

Randomization will occur at the baseline visit at a ratio of 2:1 intervention versus control. Randomization will be stratified to achieve balance in treatment allocation across idiopathic and CD-related fistula types. Because the total sample size is 12, randomization will be blocked using blocks of size 3 (2:1 intervention to control) within each stratum (idiopathic versus CD-related). Based on historical clinical data we anticipate enrolling 9 Chron’s participants and 3 idiopathic participants. Blinding of the patients, surgeons other than the investigator performing the procedure, and study team members assessing outcomes to study arm allocation will be employed to reduce bias in conducting study activities and evaluations. Given that the control group will be receiving a routine care procedure, the investigator who will be performing all procedures will be unblinded to the treatment assignment for each participant. To maintain blinding while assessing outcomes, clinical exams during follow-up study visits will be performed by another surgeon not involved in the initial screening visit or the procedural encounter. In the case of a serious adverse event or medical emergency in which knowledge of the treatment is necessary for the participant’s well-being or medical care, the unblinded investigator will be alerted to ensure appropriate medical management.

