### Statistical analysis

Categorical and binary data will be presented using counts and percentages. Continuous data will be presented using medians and interquartile ranges. All statistical tests will use an α = 0.05 Type I error rate, using two-tailed p-values as appropriate for the specified hypotheses, but 95% confidence intervals will be given primary focus above p-values (29). Statistical models will be adjusted for Crohn’s status. Model assumptions will be checked using visualizations and tests as appropriate, with data transformations and alternative models considered when assumptions are dubious.

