#### Sample Size

This study will aim to recruit and screen 60 eligible patients to enroll and randomize 12 participants in a 2:1 ratio. Sample size was influenced by expected confidence interval widths for the primary outcome (technical performance of the rhPDGF-BB-enhanced collagen implant for treatment of complex perianal fistulas). Assuming that all 8 participants assigned to the intervention arm will achieve successful implementation of the treatment, the lower bound of a Clopper-Pearson 95% confidence interval would be 0.63, indicating high confidence that the treatment does not have a low probability of successful implementation. Sample size was also influenced by the efficacy outcome of healing at 3 months. Based on the prior work in the literature, we assume that the routine care arm (across the expected distribution of routine care procedures) will achieve 50% healed at 3 months (2/4 healed). If 7 of the 8 intervention arm patients achieve healing, the expected lower bound of a Carlin-Louis 95% confidence interval for the differences in proportions healed would be about −0.14, indicating high confidence that the intervention does not cause substantial harm. Furthermore, if all 8 intervention arm patients achieve healing, the expected interval lower bound will be −0.01, such that there is high confidence of treatment benefit.

We assumed that study dropout before Month 3 will not occur, and that crossover into the intervention arm will not occur until after ascertainment of Month 3 outcomes. The time-to-healing will be considered for secondary analyses and likely have slightly higher power assuming that patient-reported data is accurate and high quality, as it achieves higher granularity to assess healing than the binary outcome of healing at Month 3 follow-up. Likewise, exploratory analyses including crossover patients may improve power for assessing the primary outcome. Other secondary endpoints and subgroup analyses are exploratory in nature, and we did not perform formal power analyses for these.

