Supplementary analysis of this secondary endpoint will consider time in weeks to achieve complete healing from baseline up to 12 weeks. This endpoint will be determined by the self-reported measure of no leakage from the weekly participant survey and will be focused on the first achievement of complete healing, as recurrence will be assessed in other outcomes. This endpoint will be analyzed using a Cox proportional hazards model, conditional on the treatment arm and Crohn’s status as outlined in the SAP. The results will be presented as an adjusted hazard ratio and a marginal hazard ratio after performing standardization. Proportional hazards will not be checked with a hypothesis test, as this is typically not a recommended procedure; instead, Kaplan-Meier curves will be calculated, and plausibility of proportional hazards will be assessed visually. If proportional hazards are violated or model fit is poor, the outcome will be compared across arms using the log-rank test. Missing data are expected to be limited, but will be handled using multiple imputation, taking the longitudinal nature of surveys into account.

The next secondary endpoint is fistula recurrence at 6 months. This will be measured as the percentage of the total number of treated participants in each arm that were diagnosed as healed at Month 3 with subsequent recurrence of the fistula by clinical evaluation of the external opening at the Month 6 follow-up visit. This is a binary endpoint which will be analyzed using the same procedures as those outlined for the binary Month 3 healing endpoint.

The final secondary endpoint is the change in the severity of symptoms at Month 3 (adjusted for baseline), which will be calculated using the ordinal scale for each question in the weekly participant survey. Scores will be compared between arms using Mann-Whitney tests. A composite variable will be calculated as defined in the SAP and analyzed using ordinal logistic regression conditional on treatment arm, baseline score, and baseline etiology. The proportional odds assumption will be assessed using a parallel line plot. A longitudinal ordinal mixed effects model with similar specification and a random intercept for study participant and a linear time term will be used to compare longitudinal symptom severity over time. Results will be presented as adjusted odds ratios and missing data will be handled using multiple imputation.

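### A visual reading of Kaplan-Meier curves from 8 v 4 participants, with no stated criterion, can replace the Crohn's-adjusted hazard ratio with an unadjusted log-rank test

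*Protocol article*

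**What the plan says.** Under Secondary and Tertiary Outcomes Analysis, the protocol article adds a supplementary analysis to the Month 3 healing endpoint: weeks to the first self-reported absence of leakage, followed to week 12. The model is Cox regression on arm and Crohn's status, and the results are an adjusted and a standardised marginal hazard ratio. A hypothesis test of proportional hazards is ruled out. Instead, "Kaplan-Meier curves will be calculated, and plausibility of proportional hazards will be assessed visually". The consequence follows: "If proportional hazards are violated or model fit is poor, the outcome will be compared across arms using the log-rank test".

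The opening of Statistical analysis sets the general rules. Confidence intervals take precedence over p-values, models are adjusted for Crohn's status, and assumptions are checked, "with data transformations and alternative models considered when assumptions are dubious".

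Sample Size gives the scale: "enroll and randomize 12 participants in a 2:1 ratio".

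**The concern.** The text states a rule: a look at the outcome curves decides which analysis of time to healing is used. Neither trigger (implausible proportional hazards or poor fit) has a criterion. With 4 control participants the control curve moves in steps of 25 points, and with 8 intervention participants the other moves in steps of 12.5. Curves this coarse can touch and cross without any departure from proportional hazards.

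At stake is the result the plan says it wants to interpret, an effect estimate with an interval, adjusted for etiology. The adjustment matters because the control procedure itself differs between idiopathic and Crohn's fistulas. The fallback supplies neither the estimate nor the adjustment.

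**Working it through.** **Inputs from the protocol article.**
- Arms of 8 and 4, from 12 participants at 2:1. The design uses "blocks of size 3 (2:1 intervention to control) within each stratum" and expects 9 Crohn's and 3 idiopathic participants, which gives exactly 8 v 4.
- Control healing of 50% at 3 months (Sample Size).
- Intervention healing in the planning case: "If 7 of the 8 intervention arm patients achieve healing", that is 87.5%.
- Dropout: "We assumed that study dropout before Month 3 will not occur".
- Weekly surveys to week 12.

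**The plan's own figures first.** The Clopper-Pearson lower bound for 8/8 is 0.025^(1/8) = 0.631 (stated 0.63). The Carlin-Louis lower bounds, taken as equal-tailed posterior intervals with uniform priors, are -0.144 for 7/8 v 2/4 (stated about -0.14) and -0.008 for 8/8 v 2/4 (stated -0.01). All three reproduce, which confirms the 8 v 4 set-up. The article gives no figure for the behaviour of the Kaplan-Meier check.

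**Simulation under exactly proportional hazards.** Healing times are exponential, with weekly hazard -ln(1 - p)/12 in an arm where a proportion p heals by week 12. Times are rounded up to whole weeks and censored at 12, with no dropout. The hazard ratio is ln(1 - p1)/ln(1 - p0):
- 50% v 50%: HR = 1.0
- 72.7% v 50%: ln(0.273)/ln(0.5) = 1.87 (72.7% is the top of the healing range quoted in the Introduction, used here as an intermediate case)
- 87.5% v 50%: ln(0.125)/ln(0.5) = 3.0

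A crossing means that each curve is strictly above the other in at least one week.

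| Intervention v control healing | HR | Any crossing | At least 25 points each way | Share of crossings where one curve never leads by more than 12.5 points |
|---|---|---|---|---|
| 50% v 50% | 1.0 | 44% | 12% | 73% |
| 72.7% v 50% | 1.87 | 41% | 14% | 65% |
| 87.5% v 50% | 3.0 | 29% | 11% | 63% |

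**Sensitivity.** Any crossing ranges over 23% to 45% with Weibull shapes 0.7 to 3, and 29% to 49% with an etiology effect of 0.5 or 2. Control healing of 30% gives 27% to 32%. Continuous rather than weekly time gives 37% to 52%. Hazard ratios of 4 to 5 at 50% control healing bring it down to 15% to 21%.

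**Role of sample size.** At 80 v 40, crossing falls to 17% at HR 2 and 3% at HR 3, but is 66% at HR 1. Small numbers explain the crossings when there is an effect. With no effect, curves cross often at any size.

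**Link to the result.** The log-rank test rejects in 1% of crossing v 9% of non-crossing trials at HR 1, and in 4% v 37% at HR 3. A reader who takes crossing as violation would therefore be sorting trials by their apparent effect.

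**What the fallback does.** The log-rank test is the score test of the Cox model with arm alone, so it is no remedy for non-proportional hazards. As written it has no Crohn's term, and it returns a p-value without an estimate or interval.

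**When a hazard ratio cannot be estimated.** The chance that no control participant heals is 0.5^4 = 6.25%. With no effect, the chance that no intervention participant heals is 0.5^8 = 0.4%. At least one arm without healing therefore occurs in about 6% to 7% of trials. Counting every pattern that makes the unadjusted hazard ratio zero or infinite, the figure is 7% to 9%.

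**The case against.** The strongest reply is that 29% to 44% is not an error rate of the plan. A reader might infer that the analysis would be switched wrongly in that share of trials. The documents do not support this, because they never name crossing as the sign of violation. Nor can each crossing be called an obvious violation: in 63% to 73% of them one curve leads by no more than one of eight participants, which someone who knows the sample size would discount. The opposite claim, that a tolerant reader would almost never switch, is not shown either, since clear two-sided crossings still occur in 11% to 14%. Truly non-proportional hazards were not simulated, so how well the plot detects them is unknown. All of this stands.

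Loss of the hazard ratio is also partly inferred. The article first says, without condition, that the hazard ratios will be presented. For logistic regression it states outright that Fisher's test substitutes for the model, and for Cox it does not. Substitution remains the likelier reading, but the text leaves it open.

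Three further inferences should be resisted:
- The 2:1 step sizes reveal the arms to whoever reads the plot, but the article promises no blinded statistician.
- The general sentence on alternative models covers every model in the trial, and nothing here tests it.
- The statistical analysis plan, not shown, may define how the plot is read. A criterion there would narrow the judgement but would not change what the log-rank fallback lacks.

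**Conclusion.** The concern holds in a limited form. The article lets an unspecified visual judgement move the time-to-healing comparison from a Crohn's-adjusted hazard ratio to a test that does not address the supposed problem, drops the adjustment and gives no interval. That conflicts with the article's own rules on adjustment and on the primacy of intervals.

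Under exactly proportional hazards, a common visual sign of violation appears by chance in about 29% to 44% of trials, and in a marked form in 11% to 14%. These figures assume 8 v 4, 50% control healing, intervention healing of 50% to 87.5%, weekly data and no dropout. The upper end reflects the absence of an effect rather than the small sample.

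The weight is minor. The analysis is supplementary to a secondary endpoint in a 12-person pilot whose primary outcome is technical performance, and the Month 3 odds ratio and risk ratio are unaffected.

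**What to change.** Reword the time-to-healing paragraph, and the statistical analysis plan to match:
- Report the Crohn's-adjusted hazard ratio and the planned marginal hazard ratio, each with a 95% interval, however the curves look, and describe them as average effects over 12 weeks.
- Show the Kaplan-Meier curves descriptively.
- Report the log-rank result alongside the hazard ratios, not instead of them.
- State in advance one objective exception for a hazard ratio that cannot be estimated, for example when no participant in an arm heals, and say what is reported then.

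Leave the general sentence on alternative models as it is.

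The cost is wording only. Trial status gives August to December 2026 for the end of data collection, so the change can be made before analysis. The downside is that if hazards truly are non-proportional, the hazard ratio is only an average and hides how the effect changes over the 12 weeks. The descriptive curves show that in part.

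### The fallback for time to healing is an unstratified log-rank test, which is weak under non-proportional hazards, drops etiology and gives no effect estimate

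*Protocol article*

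**What the plan says.** The supplementary analysis of Month 3 healing is weeks to first self-reported healing, up to 12 weeks. Secondary and Tertiary Outcomes Analysis says:

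- Main model: "This endpoint will be analyzed using a Cox proportional hazards model, conditional on the treatment arm and Crohn’s status as outlined in the SAP".
- Reported effect: "The results will be presented as an adjusted hazard ratio and a marginal hazard ratio after performing standardization".
- Trigger: "Kaplan-Meier curves will be calculated, and plausibility of proportional hazards will be assessed visually".
- Fallback: "If proportional hazards are violated or model fit is poor, the outcome will be compared across arms using the log-rank test".

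No strata and no effect measure are attached to the fallback. The Statistical analysis section gives three general rules: "Statistical models will be adjusted for Crohn’s status"; "95% confidence intervals will be given primary focus above p-values"; and, on assumptions, "with data transformations and alternative models considered when assumptions are dubious". Randomization and Blinding stratifies by etiology. The Discussion states that control care differs by etiology: a plug for idiopathic fistulas, natural healing for Crohn's fistulas.

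**The concern.** Three things change together when the fallback is used.

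1. One trigger is non-proportional hazards, yet the substitute gives every healing event the same weight as the Cox score does. That weighting is best when hazards are proportional. When hazards cross, early and late differences cancel.
2. The main model conditions on etiology; the named test does not. Etiology is the randomization stratum, it determines what controls receive, and it may well affect healing time.
3. The main model gives hazard ratios; the named test gives a p-value. That sits badly with the plan's stated preference for intervals.

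At stake is the usefulness of this analysis in the situation for which the fallback was written. The Sample Size section expects time to healing to have slightly higher power than binary healing, so the authors do expect information from it.

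**Working it through.** **Inputs from the protocol article.** 12 randomized 2:1, so 8 v 4. Expected 9 Crohn's and 3 idiopathic in blocks of 3, so 6 v 3 and 2 v 1. Control healing 50% at Month 3; intervention scenario 7/8 = 87.5%. Weekly data to week 12. No dropout before Month 3. Two-sided α = 0.05. Hazard shapes and etiology effects are not in the document; those below are assumptions.

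**The plan's own figures.** It gives no power or event count for time to healing. Its precision figures reproduce: the Clopper-Pearson lower bound for 8/8 is 0.025^(1/8) = 0.631 (stated 0.63). The Carlin-Louis lower bounds with uniform priors are −0.144 and −0.008 (stated about −0.14 and −0.01). They do not bear on this point.

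**Step 1: which model the log-rank test belongs to.** Over healing times, U = Σ(d₁ − d·n₁/n) and V = Σ d·(n₁/n)(1 − n₁/n)(n − d)/(n − 1); the statistic is U²/V. On one simulated untied 8 v 4 data set:

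| Statistic | Chi-square |
|---|---|
| Log-rank | 4.2539 |
| Score test, Cox with arm only | 4.2539 |
| Score test for arm, Cox with arm and etiology | 4.688 |
| Log-rank stratified by etiology | 3.597 |

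So the test matches the arm-only model, not the plan's adjusted one.

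**Step 2: validity.** Control hazard for 50% at week 12: ln 2/12 = 0.0578 per week. With no arm effect (8 v 4, weekly times, 4,000 runs), the test rejected in 0.054. With an assumed fourfold etiology effect and no arm effect, it rejected in 0.028 unstratified and 0.052 stratified. The plain test holds its size but becomes conservative.

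**Step 3: power when hazards cross.** Assume the intervention hazard is 2.4 times control to week 4 and 0.3 times afterwards. Cumulative hazard at week 12 in control-weeks: 2.4×4 + 0.3×8 = 12, so both arms reach 50%. Healed at week 4: 1 − exp(−2.4×4×0.0578) = 43% v 1 − exp(−4×0.0578) = 21%.

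Restricted mean weeks to healing up to week 12 (continuous time):
- Control: 0.5/0.0578 = 8.66.
- Intervention: 0.4257/(2.4×0.0578) + 0.5743×(1 − exp(−0.3×8×0.0578))/(0.3×0.0578) = 3.07 + 4.29 = 7.36.
- Difference: 1.30 weeks.

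| Design | Log-rank | Stratified log-rank |
|---|---|---|
| 8 v 4 (4,000 runs) | 0.040 | 0.043 |
| 200 v 100 (300 runs) | 0.11 | 0.11 |

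The low rejection rate is therefore not only a matter of 12 participants, and stratifying alone does not cure it. For comparison, under proportional hazards with HR = ln 0.125/ln 0.5 = 3, log-rank power at 8 v 4 is 0.28.

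**Step 4: gain and cost of stratifying (8 v 4, arm HR 3).**

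| Assumed etiology HR | Unstratified | Stratified |
|---|---|---|
| 4 | 0.21 | 0.28 |
| 0.25 | 0.16 | 0.22 |

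With no etiology effect, stratifying costs about 0.02 at HR 3 and 0.05 at HR 5. In an assumed late-effect case (same hazard to week 6, then five times control), it costs 0.21 − 0.18 = 0.03 to 0.04.

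**Step 5: would a restricted-mean test be better?** With four blocks of 3 and 3,000 runs, when the intervention heals in weeks 1–5 and controls in weeks 7–12, 85% in each arm, power was 0.29 for the log-rank, 0.37 stratified and 0.62 for a re-randomized restricted-mean difference. With fast-healing controls and slow intervention healers the order reversed: log-rank 0.20, restricted mean 0.07.

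**The case against.** Most of what can be said for the plan limits the point rather than removing it.

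- **Validity.** A reader might infer that the log-rank test carries over the failed assumption and is therefore wrong, or that it is the score test of the plan's own Cox model. Neither holds. Proportional hazards is needed for optimality, not validity (null rate 0.054), and the test corresponds to the arm-only model. If it were the score test of the adjusted model, no adjustment would be lost.
- **The other trigger.** The fallback also covers poor model fit. With 50% healing and 4 controls, no control heals with probability 0.5⁴ = 6%. The Cox estimate is then not finite, but the log-rank test can still be computed. For that trigger the test is a sensible choice.
- **General rules.** The adjustment rule speaks of models, and a log-rank test is not a model. The preference for intervals does not demand one for every test, and alternative models stay open. So this is a poor fit with the plan's own emphasis, not a formal contradiction.
- **The SAP.** Stratification can be a SAP detail. But the article names the trigger, the test and the comparison, and its reference to the SAP is attached to the Cox model. Followed as written, the rule is unstratified.
- **Something is left to report.** Kaplan-Meier curves will exist, and Month 3 healing has its own odds ratio with an interval and a marginal risk ratio. That stands. Yet the curves are planned only as an assumption check, and binary healing says nothing about speed.
- **Replacing the test.** A reader might conclude that a restricted-mean test should take over. The reversal in Step 5 shows that this is a trade-off. With an expected 2 v 1 idiopathic stratum, a variance cannot be estimated from the single control there.

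**Conclusion.** The point holds in a limited form. The fallback is a valid test of equal healing curves, but it keeps the proportional-hazards weighting, so it does not remedy non-proportional hazards. As written it also omits etiology and supplies neither an estimate nor an interval.

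The etiology gap costs about 0.06 to 0.07 in power at arm HR 3, if etiology changes the healing hazard fourfold in either direction. The weighting costs more where hazards cross: rejection of 0.040 at 8 v 4 and 0.11 at 200 v 100, despite a true difference of 1.3 weeks. These figures rest on assumed shapes. Even under proportional hazards, 12 participants give power of only 0.28, so low power is not mainly the fallback's doing.

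The consequence for the trial is small. The rule applies only if a visual check or poor fit triggers it, in a supplementary, self-reported analysis of a secondary endpoint. It touches neither the primary outcome nor the clinical Month 3 healing analysis.

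**What to change.** Revise the fallback sentence in Secondary and Tertiary Outcomes Analysis, and the SAP to match, before outcome curves by arm are seen:

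1. Stratify the fallback log-rank test by etiology.
2. Report beside it an estimate that does not need proportional hazards, with a 95% interval. One example is the difference in restricted mean weeks to healing up to 12 weeks. It accompanies the test and does not replace it. State how the interval is obtained, given the expected 2 v 1 idiopathic stratum.
3. Do not describe the log-rank test as a remedy for non-proportional hazards. Keep it for the poor-fit trigger as well.

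The cost is one or two sentences and a few lines of code. The downsides are a small loss of power if etiology does not affect healing time (about 0.02 at HR 3, 0.05 at HR 5) and an interval that will be wide with 12 participants.

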## METHODS

### Trial design

This study will be carried out in accordance with International Conference on Harmonisation Good Clinical Practice (ICH GCP) and the United States (US) Code of Federal Regulations (CFR) applicable to clinical studies (45 CFR Part 46, 21 CFR Part 50, 21 CFR Part 56, 21 CFR Part 312, and/or 21 CFR Part 812). This Phase II clinical trial will evaluate the performance, preliminary safety and efficacy, and feasibility of rhPDGF-enhanced collagen on healing complex perianal fistulas that are not eligible for a fistulotomy in patients 21 years of age and older. This prospective, blinded, single-site study is expected to enroll and randomize 12 participants at a 2:1 intervention versus control allocation ratio stratified by fistula etiology, idiopathic versus CD-related. The two arms will compare implantation of the rhPDGF-enhanced collagen to routine care procedures, which include COOK Biotech’s Biodesign^®^ Anal Fistula Plug implant for idiopathic fistulas or draining seton removal and natural healing for CD-related fistulas. Following the baseline procedure, patients will be evaluated at Months 1, 3, and 6 to assess healing of the external fistula opening and change in pain, incontinence, and other perianal fistula-related symptoms. Patients randomized to the control group who fail to heal at Month 3 will have the option to crossover to the intervention group and receive the rhPDGF-enhanced collagen intervention. The Standard Protocol Items: Recommendations for Interventional Trials (SPIRIT) schedule of enrollment, intervention, and assessments is included as Figure 1. A graphic study timeline of events is provided in Figure 2. The SPIRIT checklist is included in S1 Appendix. A full accounting of evaluations and unabridged protocol approved by the IRB is available in S2 Appendix (December 13, 2024; version 6.1) and important protocol modifications will be available from the corresponding author and by viewing the ClinicalTrials.gov (NCT06632418) study entry. A sample consent form is included in S3 Appendix.

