#### Secondary outcomes

The secondary outcomes of this study will be used to assess the preliminary safety and efficacy of rhPDGF-enhanced collagen for treatment of complex perianal fistulas. A quantitative and descriptive summary of all intervention-related adverse events (AEs) within 3 months of the procedure will be used to assess preliminary safety. Clinical evaluation of fistula healing assessed as healed/not healed by no drainage/drainage from the external opening at the Month 3 follow-up visit will determine the proportion of fistulas healed. Rate of recurrence is assessed by the number of participants with clinically diagnosed healed fistulas (no drainage/no leakage) that are later diagnosed with recurrence at the final, Month 6 study visit. The Month 6 endpoint was chosen because successful treatment of complex perianal fistulas is based not only on a diagnosis of being completely healed by clinical exam but also on clinical remission without recurrence, and the majority of recurrences occur within 6 months of the treatment. Safety and efficacy will also be assessed by the change in patient-reported pain, incontinence, and other perianal fistula-related symptoms in the baseline and weekly follow-up participant surveys.

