### Study Assessments and Procedures

#### Safety Assessments

Clinical examination
At screening, during the procedure, and at all follow-up visits, clinical examination of the perianal fistula will visually assess for infection, excess drainage, chronic inflammation, abnormal bleeding, or fibrosis at the external opening. Photographs of the external openings will be taken at screening and all follow-up visits to document healing progress.Patient medical history
At screening, patients meeting inclusion criteria will be screened for exclusion criteria through their medical history. The etiology of the perianal fistula will also be discussed and documented. Participants will review any known allergies, previous surgical procedures, previous complications, and frequency of fistula occurrence or recurrence.Pregnancy test
At screening, women of childbearing potential will be required to take a pregnancy test and must agree to use two reliable contraceptive methods for the duration of their participation in the study, one of which must be a barrier method; the contraceptive methods will be documented in the screening eCRFs.Crohn’s Concomitant Medications
At screening and all follow-up visits, Crohn’s medications will be documented for patients with CD-related perianal fistulas, including medication name, single dose amount, route, frequency, start date, and end date.Participant survey
At screening, baseline, and weekly following the procedure till Month 3, participants will complete a self-report questionnaire assessing the frequency and severity of pain, incontinence, and other perianal fistula-related symptoms. If symptoms are increasing in frequency and severity, an off-cycle clinical visit will be scheduled to address any adverse events.Assessment of adverse events
The following adverse events will be recorded in the eCRFs and followed until resolution:
Adverse events that are classified as related to study procedures (that is, potentially-, probably-, or definitely related to study procedures or of uncertain relationship to study procedures), regardless of severitySerious adverse events regardless of relatedness to study procedures.Clinical adverse events, events diagnosed as clinical conditions, with a severity grade ≥ 3, regardless of relatedness to study procedures.

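### Read literally, the recurrence endpoint scores only the Month 6 exam, so a recurrence that was re-treated and is dry again at Month 6 counts as no recurrence, and one followed by a missed Month 6 visit is imputed instead of counted

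*Protocol article*

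**What the plan says.** The protocol article defines recurrence twice, and the two definitions agree. Under Secondary outcomes, it is the number of participants with healed fistulas "that are later diagnosed with recurrence at the final, Month 6 study visit". Under Secondary and Tertiary Outcomes Analysis, it is the percentage healed at Month 3 with "subsequent recurrence of the fistula by clinical evaluation of the external opening at the Month 6 follow-up visit".

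Secondary outcomes explains the timing: treatment success rests on a healed exam and also on "clinical remission without recurrence, and the majority of recurrences occur within 6 months of the treatment".

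Three other statements bear on the interval between Month 3 and Month 6:

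- Trial design: "patients will be evaluated at Months 1, 3, and 6". No visit is scheduled in between.
- Safety Assessments: the participant survey is completed "weekly following the procedure till Month 3". If symptoms worsen, "an off-cycle clinical visit will be scheduled to address any adverse events".
- Secondary and Tertiary Outcomes Analysis: recurrence is analysed by the procedures given for Month 3 healing. Those handle missing outcomes by multiple imputation, and for participants lost before Month 3 they name baseline data, the Month 1 assessment and weekly symptom data as the conditioning information.

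**The concern.** Remission without recurrence is a statement about an interval: it fails once a recurrence has happened, whatever is done afterwards. The rule records a state at one time point. The two agree unless the state changes back before the exam or the exam does not take place.

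The article gives no path from an interval diagnosis to the endpoint. The survey has stopped by then. The off-cycle visit is attached to that survey and serves adverse events. A recurrence at Month 4 or 5 might be recorded as an adverse event, but no rule carries it into the recurrence count.

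Recurrence is the only efficacy endpoint assessed after Month 3, and the Discussion says the trial should guide a larger one. The participants at risk of being misread are those whose recurrence was bad enough to bring them to care before Month 6. With so few healed participants expected, one such record can remove all observed recurrence from an arm.

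**Working it through.** **The plan's own figures.** The article states no recurrence rate and no precision for recurrence, so there is no figure to reproduce for this endpoint. The Sample Size figures do reproduce. The Clopper-Pearson lower bound for 8/8 is 0.025^(1/8) = 0.631 (stated 0.63). With Beta(1,1) priors, the lower bounds for the difference in healing are -0.144 for 7/8 against 2/4 (stated about -0.14) and -0.008 for 8/8 against 2/4 (stated -0.01). They concern implantation and healing and do not bear on recurrence. Only the healing scenario is carried forward: 7 of 8 intervention and 2 of 4 control participants healed at Month 3.

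**Four records scored by the literal rule.** All four participants are healed at Month 3.

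| Record | Month 3 to 6 | Month 6 exam | Score under the rule | Remission without recurrence? |
|---|---|---|---|---|
| A | nothing | dry | no recurrence | yes |
| B | recurrence diagnosed at Month 4 | still draining | recurrence | no |
| C | recurrence diagnosed at Month 4, re-treated | dry | no recurrence | no |
| D | recurrence diagnosed at Month 5 | not done | missing, so imputed | no |

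Record B is scored correctly. Record C receives the same score as A. In record D a known event is replaced by a random draw. The named predictors (baseline, Month 1, weekly symptoms up to Month 3) all precede the recurrence, and this participant was judged healed after most of them were collected. The section on discontinuation and withdrawal makes D possible: an investigator may withdraw a participant for an infection or abscess requiring plug removal, or for disease progression.

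**Effect of one record of type C.** The shift is 1/n, where n is the denominator. Intervals are 95% Clopper-Pearson.

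| Arm and denominator | Event counted | Event missed | Shift |
|---|---|---|---|
| Intervention, 7 healed | 1/7 = 14.3% (0.4% to 57.9%) | 0/7 = 0% (0% to 41.0%) | 14.3 points |
| Control, 2 healed | 1/2 = 50% (1.3% to 98.7%) | 0/2 = 0% (0% to 84.2%) | 50 points |
| Intervention, 8 treated | 1/8 = 12.5% | 0/8 = 0% | 12.5 points |
| Control, 4 treated | 1/4 = 25% | 0/4 = 0% | 25 points |

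The last two rows apply if all treated participants form the denominator.

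**Dependence on frequency (illustration only).** Let r be the true recurrence between Months 3 and 6, and s the share of recurrences that are dry again at an attended Month 6 exam. The recorded rate is r × (1 - s). Neither input is in the document. For r assumed from 10% to 40%, the recorded rate runs from 7.5% to 30% at s = 0.25, and from 5% to 20% at s = 0.5. At s = 0 nothing is lost.

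**The case against.** **A reader might infer that every recurrence diagnosed and treated between Months 3 and 6 is scored as no recurrence.** The document does not support this. One that is still open or draining at Month 6 is visible at the exam and counts.

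**A reader might also infer that a participant withdrawn before Month 6 is scored as recurrence-free, so that the rule can only lose events.** Also not supported. The outcome would be missing and multiply imputed, and a draw can be a recurrence. The fault there is narrower: a diagnosed event is not used.

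**Loss may be uncommon.** The only re-treatment path described, for crossovers, places a seton for about 4 weeks before the procedure, and Primary outcome puts the average judgement of healing at 3 months. Together these exceed the 3 months from Month 3 to Month 6. This argues against assuming a high frequency. It does not exclude record C, because 3 months is an average time to a final judgement and not the shortest time in which an opening can be dry at one exam.

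**A fixed exam protects blinding.** Follow-up exams are done by a surgeon not involved in screening or the procedure, while an interval diagnosis may come from an unblinded clinician. This is a real cost of the change, and a sensitivity analysis can meet it.

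**The full protocol or the SAP may hold a rule for interval events.** They may, and neither is shown. But the article itself fixes how and when recurrence is judged. For this endpoint it does not defer to the SAP, as it does for the Cox model and the symptom composite. The point concerns what that stated rule yields.

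**Conclusion.** The point holds in this limited form. Taken literally, the definition scores a recurrence that was re-treated and is dry again at Month 6 as no recurrence, and it imputes a recurrence diagnosed before a missed Month 6 visit instead of counting it. Neither result matches the stated aim of remission without recurrence. The two definitions do not contradict each other; the mismatch is between both of them and the reason given for Month 6.

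The size per event rests only on the plan's healing scenario: 14 points in the intervention arm or 50 in the control arm among healed participants. Those large steps reflect the small arms, and any single misclassification would produce them. The expected number of such events, and hence the overall bias, cannot be derived from the document. The endpoint is secondary and has no formal power calculation, so this is a correction worth making before analysis and not a threat to the primary result.

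**What to change.** In Secondary outcomes and in Secondary and Tertiary Outcomes Analysis, define recurrence as any clinically diagnosed recurrence of, or re-intervention on, the target fistula after the Month 3 healed assessment up to and including the Month 6 visit. Record the date of diagnosis. State that a documented interval recurrence counts as an event even if the Month 6 visit is missed, and keep multiple imputation for participants whose status through Month 6 is truly unknown. Report the blinded Month 6 exam result alone as a sensitivity analysis.

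The cost is a sentence or two in the endpoint definition, one eCRF question at Month 6 on interval recurrence or procedures, and a chart check at the single site. The downside is that some interval diagnoses may be made by an unblinded clinician, which the sensitivity analysis makes visible. The change affects how events are counted and not how participants are treated. The article describes the trial as ongoing, with data collection ending between August and December 2026, so the change could be made before analysis.
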